#### Participant timeline

Household visits for the questionnaire will occur at dry season and rainy season baseline and at endline (Figs. 1 and 2). The seroprevalence baseline and follow-up surveys will occur yearly (for 3 years), 5 months after the rainy season peak to allow the maximum levels of IgG to be reached without residues of other immune reactions to cross-react [50]. A baseline entomological survey will occur in rainy season, the same period as the household questionnaire. Following baseline, entomological surveys will occur yearly during the rainy season. Community focus groups and interviews will occur twice a year, starting with the baseline assessment.

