## Objectives

The principal research question of this study is: does community mobilization reduce the risk of dengue virus (DENV) infection compared to usual dengue control practice in Fortaleza, Brazil? The specific objectives are 1) Measure the impact of the intervention on the risk of primary dengue infections using serological indicators in participating children; 2) Measure the impact of the intervention on human exposure to adult female *Aedes* in participating households; 3) Measure the impact of the intervention on self-reported dengue in participating households; 4) Explain the heterogeneity of the effect of community mobilization; 5) Analyze the acceptability of the intervention and the empowerment process of communities and individuals.

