### Trial design

We will follow a parallel pragmatic cluster randomized controlled trial (cRCT) design with randomization at the census tract level with equal allocation to the two arms, to evaluate the effectiveness of community mobilization measured by the risk of primary DENV infection, self-reported dengue cases, and *Aedes* infestation rates. The quantitative baseline assessment will include a household questionnaire, entomological evaluation of households and high-risk communal areas, and blood samples (from finger pricks) from children aged 3–9 years. Following the baseline assessment, allocation will occur after which community mobilization activities will begin for a period of 24 months. Baseline community interviews and focus groups for the qualitative studies will be performed just after allocation.

This is an investigator-initiated trial that was registered with ISRCTN66131315 prior to enrollment. The trial protocol was developed according to the Standardized Protocol Items: Recommendations for Interventional Trials (SPIRIT) guidelines (Additional file 1) [35].

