### Methods: participants, interventions, and outcomes

#### Study setting

The city of Fortaleza, capital of Ceará State, is situated on the Atlantic coast of north-eastern Brazil with a rainy season from January to May. Fortaleza is vulnerable to infestation of *Aedes aegypti* due to its tropical climate, high population density and rapid population growth (4.9%; from 2010 to 2014 [36]), and inadequate sanitary conditions [33, 37]. Irregular water supply leads people to store water in various containers such as water tanks, cisterns, barrels, drums, bowls, and pots. Fortaleza is particularly burdened by arboviruses. From 2016 to 2017, there were 35,159 cases of dengue, 79,486 cases of chikungunya, 1598 cases of zika, and 52 cases of congenital zika syndrome reported in Fortaleza [31, 32, 38]. It is important to note zika cases began to appear in large numbers in Fortaleza in 2015 although the compulsory notification did not begin until 2016. There are two currently circulating dengue serotypes in Fortaleza, DENV1 and DENV2 [39], with the public health officials anticipating the possibility of reintroduction of DENV3 within the next few years.

Standard dengue control practice activities of the Fortaleza Municipal Health Secretariat include periodic visits of houses and high-risk *Aedes* breeding grounds in communal areas (e.g., scrapyards, tire repair shops, etc.) by vector control agents for habitat destruction and application of the larvicide, Diflubenzuron, for containers that cannot be cleaned [40]. In Brazil, the use of temephos as a larvicide was discontinued in 2010 due to increased resistance and toxicity and the general population of Fortaleza do not have access to larvicides for domestic purposes. The Vector Control Department within the Fortaleza Municipal Health Secretariat is responsible for community education and mobilization actions in areas of higher transmission risk.

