#### Outcomes

Primary outcomes are: rates of anti-dengue Immunoglobulin G (IgG) seroconversion (from negative to positive at follow-up) to evaluate the incidence of primary infections, and adult female *Aedes* density (number of adult female *Aedes* per household). Additional measurement of the antibodies waning rate or disappearance of detectable IgG antibodies (from positive at baseline to negative at follow-up), which may happen one to 2 years after primary dengue infections will determine the impact of the intervention on subsequent dengue secondary infections [48]. Secondary outcomes captured during household visits at baseline and follow-up are: i) anti-dengue IgG antibodies waning rates; ii) self-reported dengue during the most recent dengue season; iii) entomological indices: the container index (number of positive containers per household) and the premise condition index (how well the structure is maintain and yard), and, iv) knowledge, attitudes, and practices (KAP) for dengue control that will combined to create an index [49]. Secondary outcomes captured from the household survey, community focus groups, and in-depth individual interviews include: i) social acceptability of activities; ii) implementation fidelity and adaptability processes; iii) potential for sustainability, and iv) empowerment of individual and communities.

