#### Allocation

After both baseline collections, the rate of IgG seroconversion of each cluster will be calculated. Based on the overall distribution of seroconversion rate, there will be five risk strata created and each cluster from the baseline assessment will then be assigned to a risk stratum. A computer generated (block) randomization of each enumerated member of the strata will be assigned to either the intervention or control arm.

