#### Household survey

A questionnaire will be administered to a principal adult respondent by a trained interviewer during the entomological inspections and will include questions about: sociodemographics; recent dengue episodes; KAP [49] with respect to dengue and dengue control practices; social capital; acceptability [65] and participation in research activities. The wet season baseline will be shorter in length, focusing on recent dengue episodes and KAP.

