## Trial status

Recruitment of participants began on 15 November 2019 and will be completed by 30 June 2020. The protocol version number is COESA-FORTALEZA-2019, dated 15 December 2019.

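### As scheduled, self-reported dengue is recorded for at most one of the two rainy seasons that follow allocation

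*Protocol article*

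**What the plan says.** All references are to the protocol article.

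- **Objectives**, third specific objective: "Measure the impact of the intervention on self-reported dengue in participating households". The Trial design section also names self-reported cases among the measures of effectiveness.
- **Outcomes**: the secondary outcome is "self-reported dengue during the most recent dengue season".
- **Participant timeline**: "Household visits for the questionnaire will occur at dry season and rainy season baseline and at endline". The same section puts blood surveys yearly, five months after the rainy-season peak, and post-baseline entomological surveys yearly in the rainy season.
- **Trial design**: after baseline, "allocation will occur after which community mobilization activities will begin for a period of 24 months".
- **Allocation**: "After both baseline collections, the rate of IgG seroconversion of each cluster will be calculated", so allocation follows both baseline rounds.
- **Household survey**: "A questionnaire will be administered to a principal adult respondent by a trained interviewer during the entomological inspections".
- **Study setting**: Fortaleza is described "with a rainy season from January to May".
- **Trial status**: "Recruitment of participants began on 15 November 2019 and will be completed by 30 June 2020".

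**The concern.** One interview after allocation, asking about one season, cannot cover two seasons of exposure. An episode in a season that is never asked about cannot be recovered in the analysis, so this is a matter of data collection and not something an analysis plan can repair.

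Objective 3 stands to lose events, and so precision. It also depends on one year's transmission: if the season captured is a quiet one, the comparison carries little information even if the other season was active.

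A lesser issue is the timing of endline. The Household survey section attaches the questionnaire to the entomological inspections, and after baseline these fall in the rainy season. A respondent interviewed then could take the most recent season to mean the one under way or the one a year earlier.

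**Working it through.** **1. Seasons after allocation**

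Inputs: 24 months of intervention (Trial design), allocation after both baselines (Allocation), recruitment ending 30 June 2020 (Trial status), rainy season January to May, five months (Study setting). The protocol does not define the dengue season by month; I take it to be the rainy season.

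- Any 24-month window contains 2 × 5 = 10 rainy-season months.
- A window that starts in any month from June 2020 to January 2021 contains exactly two complete seasons, 2021 and 2022. A start in April or May 2020, or in February 2021, would contain one complete season and parts of two others, still 10 months in all.

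**2. Seasons recorded**

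- Questionnaires after allocation: 1 (endline).
- Seasons recalled per questionnaire: 1.
- Coverage: at most 1 of 2 seasons, or 5 of 10 rainy-season months. If both seasons have equal incidence, that is half of the expected episodes.

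This does not depend on the endline month. An endline after the second season records the second only. An endline during it records either the unfinished second season or the first.

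**3. What this might mean for power (illustration only)**

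The protocol gives no risk or ICC for self-reported dengue. Its one calculation is for seroconversion, and it reproduces:

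- n per arm = (1.960 + 0.842)² × (0.30 × 0.70 + 0.2115 × 0.7885) / 0.0885² = 377.6
- design effect = 1 + 59 × 0.07 = 5.13
- clusters per arm = 377.6 × 5.13 / 60 = 32.3, against the stated 32

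For self-report I assume the same 32 clusters of 60 per arm and the same 29.5% relative reduction in each season. I also assume independent seasons and the two-sided 0.05 test of two proportions with n = 1920 / [1 + 59 × ICC]. With control risk r per season, the two-season risks are 1 − (1 − r)² and 1 − (1 − 0.705r)². For r = 0.10 these are 0.190 and 0.136, against 0.100 and 0.0705 for one season. Both ICCs below appear in the Sample size section, for seroconversion.

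| Assumed control risk per season | ICC 0.03: one season | ICC 0.03: two | ICC 0.07: one season | ICC 0.07: two |
|---|---|---|---|---|
| 0.02 | 13% | 22% | 9% | 14% |
| 0.05 | 27% | 48% | 17% | 29% |
| 0.10 | 50% | 78% | 30% | 52% |
| 0.15 | 69% | 92% | 44% | 70% |

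The levels are not forecasts. The gain from a second season appears in every row.

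**4. Would the yearly blood visit fall after the season?**

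Five months after a peak anywhere in January to May falls in June to October, so the season is over by then. The Statistical methods section lists a baseline, a first and a second follow-up, which is one follow-up blood round per post-allocation season.

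**The case against.** **More questionnaires may be intended.** The Outcomes section says these outcomes are captured at baseline and follow-up. The Document analysis section mentions household data collection every six months, the participant retention section counts four follow-up visits, and the Data monitoring section foresees six-monthly analyses. Figures 1 and 2, which I could not see, may show interim rounds and the endline month. This stands as a reason to ask for clarification. But none of these sections places a questionnaire at an interim visit, and two blood rounds plus two entomological rounds would already make four. If repeat questionnaires are meant, the Participant timeline section contradicts that and has to be reconciled.

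**One season may be deliberate.** Short recall is sensible for self-report by participants who know their arm, the last season shows the intervention at its most mature, and yearly serology covers infection across the whole period. All of this is fair, and it is why the point is confined to a secondary outcome. It does not justify leaving the other season unasked when a home visit already takes place after it.

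**Stronger readings that the documents do not support.**

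- A reader might infer that the captured season is certainly cut short, and scale the loss beyond one half. No section gives the endline month, and the tie to rainy-season inspections is loose. A dry-season baseline questionnaire is scheduled although the only baseline inspection listed is in the rainy season, and the Recruitment section lets questionnaires accompany entomological or blood collection.
- A reader might infer that baseline and endline cannot be compared. The Household survey section has the wet-season baseline ask about recent dengue episodes, so a rainy-season endline would have a same-season counterpart.
- A reader might infer bias between arms. Schedule and recall wording are the same in both arms, and nothing suggests that interview dates would differ by arm.

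**Conclusion.** The point holds in limited form. Followed as written, the schedule records self-reported dengue for at most one of the two seasons after allocation, about half of the expected episodes if the seasons are equal. That rests on reading the Participant timeline section literally, on equating the dengue season with January to May, and on allocation falling after the 2020 rainy-season baseline.

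The consequence is lower precision for Objective 3 and dependence on one season's transmission. An incomplete or ambiguous recalled season is a possibility, conditional on a rainy-season endline, and no size can be put on it from the documents. The primary outcomes and the sample size are not affected. It is worth changing because a lost season cannot be restored later and the remedy is cheap.

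**What to change.** 1. Add the dengue-episode items to each yearly blood-collection household visit after the rainy season.
2. Ask about a named, completed season (for example January to May of a stated year) in both arms and in every round, baseline included. A window from 1 January to the visit date would not do: its length changes with the visit, and enrolment from November 2019 crosses the new year, so it would run from over ten months for a mid-November interview to weeks for one in January. If the dengue season is taken to extend beyond May, the named months should say so.
3. Define the Objective 3 outcome as any self-reported episode across both post-allocation seasons.
4. State the endline month, and reconcile the Participant timeline section with the Outcomes, Document analysis and participant retention sections on which follow-up visits carry the questionnaire.

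The cost is a few minutes at visits already planned, and recall over several months. Households that miss one of the two rounds will have a partly observed outcome, which the analysis will need to handle.

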**Fig. 1 Fig1:**
[figure not shown]
Summary of research activity timeline

**Fig. 2 Fig2:**
[figure not shown]
Overview of enrolment, intervention, and assessment as per the Standard Protocol Items Recommendations for Interventional Trials (SPIRIT) Statement

#### Sample size

Our pilot data, along with a research member’s (NA) RCT in Mexico and Nicaragua facilitated the sample size estimation. Our primary outcome of interest is risk of dengue seroconversion in 3 to 9 years old. The local pilot study’s intraclass correlation coefficient (ICC) was 0.08 across the 10 control clusters and the control group risk of seroconversion was approximately 0.30 (population 5–15 years old). The community mobilization RCT for dengue prevention by Andersson et al. [7] determined an ICC of 0.03 across 150 clusters for dengue seroconversion in children aged 3 to 9 and a relative risk reduction of 29.5% (95% CI 3.8 to 55.4). Using the approach of Reich et al. [51] for finding sample sizes to compare proportions between group, assuming a risk of seroconversion of 0.30 in the control group and 0.2115 in the intervention group (based on relative risk reduction of 29.5%) and an ICC of 0.07, for 80% power, a significance level of 0.05 and 60 individuals per cluster, 32 clusters are required in each arm. An additional two clusters per arm will be added, in the event that a cluster is removed from the study due to violence creating unsafe conditions for field staff [37, 52]. To have a sufficiently powered analysis in the case of a 30% attrition rate of participants, 60/0.7 = 86 individuals per cluster per arm are required. There will be a total of 5848 participants recruited for this study (86 individuals/cluster × 68 clusters).

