#### Eligibility criteria

During enrollment visits, all households in selected clusters with children from 3 to 9 years will be eligible and asked to participate in the trial [41]. Eligibility will be evaluated on three levels: cluster, household, and individual. The inclusion criteria will be: 1) any of the 3020 census tracts from the 2010 Census; 2) households permanently inhabited; 3) children aged 3 to 9 years. The exclusion criteria will be: 1) census tracts where interventions outside of vector control standard practices occurred within the last 5 years; 2) census tracts deemed to be too insecure for study personnel (determined based upon the opinion of the research team and stakeholders); 3) clusters with less than 230 households as previous work has shown that 230–240 households are required to obtain the needed sample size [8]; 4) abandoned or non-permanent households; 5) households with the intention to move outside of the household during the study period; 6) children with chronic disease or other health condition that preclude participation in the study; and 7) parents or guardians who are unable to give informed consent.

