#### Approach for participant retention

Based on experience in pilot work ranging between 10% [7] to 20% [45] loss to follow-up with 2 visits, we have estimated a 30% rate of attrition in the current study, due to increased length of follow-up (4 follow-up visits). Participation and follow-up will be encouraged by offering at-home visits and the possibility of rescheduling visits when necessary. All data collection milestones will be scheduled in consultation with the local steering committee to determine the best possible time for the community. Advertisement will be made within the community prior the home visits for data collection to inform households of the upcoming visit of the research team. To compensate for losses due to attrition, decreased participation, and potential biological sample losses, we plan a 43% increase in recruitment.

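### The power calculation counts all 60 retained children per cluster as able to seroconvert, although only baseline IgG-negative children can, so the stated 80% needs qualifying

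*Protocol article*

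**What the plan says.** The Outcomes section defines the serological primary outcome as "rates of anti-dengue Immunoglobulin G (IgG) seroconversion (from negative to positive at follow-up) to evaluate the incidence of primary infections". The Eligibility criteria set no condition on serostatus: "all households in selected clusters with children from 3 to 9 years will be eligible". The Background calls the setting hyperendemic, and the Outcomes section makes antibody waning in children who are positive at baseline a secondary outcome. So IgG-positive children are expected in the cohort.

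The Sample size section works from "assuming a risk of seroconversion of 0.30 in the control group and 0.2115 in the intervention group", an ICC of 0.07, and the conclusion that "for 80% power, a significance level of 0.05 and 60 individuals per cluster, 32 clusters are required in each arm". It then makes two additions:
- "An additional two clusters per arm will be added, in the event that a cluster is removed from the study due to violence", giving 34 per arm.
- "in the case of a 30% attrition rate of participants, 60/0.7 = 86 individuals per cluster per arm are required", giving 5848 children over 68 clusters.

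The section on participant retention describes the same increase in these words: "To compensate for losses due to attrition, decreased participation, and potential biological sample losses, we plan a 43% increase in recruitment".

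**The concern.** A child who is IgG-positive at baseline cannot go from negative to positive. Yet the calculation applies the two seroconversion risks to all 60 children retained per cluster, as though every one were at risk. The 43% increase is the same thing as 60/0.7, and 30% attrition consumes it entirely. The retention section also charges participation and sample losses to it. Neither section allows for children who are already seropositive.

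If the 0.30 is a risk among susceptible children, the informative number per cluster is below 60 and the power is below the figure printed. A null result would then be read against 80% power when the true figure could be several points lower.

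**Working it through.** **Inputs.** From the Sample size section: p1 = 0.30, p2 = 0.2115, ICC = 0.07 (local pilot 0.08, earlier multi-site trial 0.03), 60 analysed children per cluster, 32 clusters per arm plus 2 spare, attrition 30%. Alpha 0.05 is taken as two-sided. Assumed, because the documents give no figure: the share s of retained children who are IgG-negative at baseline.

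**Reproducing the plan.**
- Individual n per arm = 7.849 × (0.30×0.70 + 0.2115×0.7885) / 0.0885² = 7.849 × 0.37677 / 0.0078323 = 377.6.
- Design effect = 1 + 59×0.07 = 5.13.
- Clusters per arm = 377.6 × 5.13 / 60 = 32.3, in line with the stated 32.
- 60/0.7 = 85.7, so 86; 86/60 = 1.43; 86 × 0.7 = 60.2; 86 × 68 = 5848.

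Power at m at-risk children in each of c clusters: n_eff = m·c / (1 + (m−1)·ICC), and power = Φ(0.0885/√(0.37677/n_eff) − 1.96). With m = 60 and c = 32, n_eff = 1920/5.13 = 374.3 and power is 79.7%. The pooled-variance version gives 79.4%. The plan's figure therefore reproduces with all 60 children at risk.

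**Replacing 60 by 60·s, all else unchanged, ICC 0.07.**

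| IgG-positive (assumed) | At risk per cluster | Design effect | Power, 32 clusters | Power, 34 clusters |
|---|---|---|---|---|
| 0% | 60 | 5.13 | 79.7% | 82.0% |
| 20% | 48 | 4.29 | 77.9% | 80.3% |
| 30% | 42 | 3.87 | 76.6% | 79.1% |
| 50% | 30 | 3.03 | 72.8% | 75.3% |
| 70% | 18 | 2.19 | 64.7% | 67.4% |

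Example, 50% row: n_eff = 30×32/3.03 = 316.8; 0.0885/√(0.37677/316.8) = 2.566; Φ(2.566 − 1.96) = 72.8%.

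**At the local pilot ICC of 0.08.** With 50% positive, the design effect is 1 + 29×0.08 = 3.32 and power is 68.9% (32 clusters) or 71.5% (34). Part of that drop comes from the ICC alone. With nobody positive, the design effect is 5.72, n_eff is 1920/5.72 = 335.7, and power at 32 clusters is already 75.2%.

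**Offsets.**
- ICC 0.03, 50% positive, 32 clusters: design effect 1.87, n_eff = 960/1.87 = 513.4, power about 90%.
- Attrition 10%, 40% positive: 86×0.9×0.6 = 46.4 at risk; power 77.6% (32 clusters) or 80.0% (34).
- Attrition 20%, 30% positive: 86×0.8×0.7 = 48.2 at risk; power 77.9% or 80.3%.

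**The case against.** The strongest reply is that the denominator of the 0.30 is not stated. The protocol attributes it to the local pilot, in ages 5 to 15. If it was the share of all tested children who converted, positives included, then 60 children per cluster is coherent and the point falls away. This stands as a possibility. A risk of negative-to-positive conversion is more naturally a risk among negatives, but the text does not settle the matter.

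Second, the loss is blunted and may be offset. At ICC 0.07, extra children per cluster add little, so halving the number at risk costs about 7 points (79.7% to 72.8%). With all 34 clusters kept, power stays at about 80% up to about 20% positive. The retention section cites pilot losses of only 10% to 20%, and the earlier trial's ICC was 0.03. Stratified allocation may also reduce between-cluster variance. All of this stands, with limits: the spare clusters are held against losses to violence, the protocol itself plans for 30% attrition over more visits, and the ICC it chose is 0.07.

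Third, a reader might try to derive seroprevalence from the 0.30 itself. Read as a constant hazard over two years, it would leave only about a third of these children IgG-negative. The documents do not support that step. The accrual period is unstated, the figure comes from an older age range, and the model assumes no waning, whereas the Outcomes section says detectable IgG may disappear one to two years after a primary infection. Changing the assumed period from two years to five moves the negative share from about 33% to about 64%.

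**Conclusion.** The mismatch is real: the outcome can occur only in IgG-negative children, enrolment ignores serostatus, and nothing in the calculation allows for children already positive. If the 0.30 is a risk among negatives, then at ICC 0.07 and 30% attrition the printed power holds at 32 clusters only with almost no IgG-positive children, and at 34 clusters with up to about 20%. Over the assumed range of 20% to 70% positive, power runs from about 78% down to 65% with 32 clusters, and from 80% down to 67% with 34.

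A reader might conclude that the trial never had 80% power. The documents do not show that: they give no seroprevalence, leave the denominator and period of the 0.30 open, and report ICCs that put power on either side of 80%. Nor is this an arithmetic slip, since 32, 86 and 5848 all reproduce. It should be fixed, as a matter of stating the right denominator. The outcome, randomisation and analysis are unaffected.

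**What to change.** 1. State the denominator (IgG-negative children or all children tested) and the accrual period of the 0.30 risk.
2. Base the calculation on the expected number of retained IgG-negative children per cluster, giving the assumed baseline share.
3. Replace the unqualified 80% with power computed from the observed number of IgG-negative children in the baseline serosurvey. Do this before allocation, at ICC 0.07 and at the pilot's 0.08.

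Do not restate the requirement as 60 IgG-negative children per cluster. That would mean recruiting 60/(0.7×0.8) = 107 per cluster at 80% negative, or 60/(0.7×0.5) = 171 at 50%, against the planned 86.

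The cost is a recalculation from data the trial already collects before allocation, with no extra children. The downside is that the stated power will probably look less favourable.
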